# Jakyakgamcho-tang in the relief of delayed-onset muscle soreness in healthy adults: study protocol for a randomized, double-blind, placebo-controlled, crossover design clinical trial

**DOI:** 10.1186/s13063-020-4119-4

**Published:** 2020-02-21

**Keywords:** Delayed-onset muscle soreness, Herbal medicine, Jakyakgamcho-tang, Peony licorice decoction, Shakuyakukanzoto, Shaoyaogancao-tang

## Abstract

**Background:**

Muscle soreness after exercise, called delayed-onset muscle soreness (DOMS), may cause significant changes in muscle function and may increase the risk of sports injuries. Therefore, various therapeutic strategies have been studied to help recovery after exercise. Jakyakgamcho-tang (JGT) is a widely prescribed herbal medicine to treat muscle pain and cramps in traditional Eastern medicine. The aim of this study is to evaluate the effect of JGT for reducing pain and improving muscle damage after exercise.

**Methods:**

This study is a randomized, double-blind, placebo-controlled, crossover design clinical trial. A total of 30 healthy male adults will be recruited. Subjects who voluntarily wish to participate in this study will be hospitalized for 4 days. On the first day, the subjects will perform a standardized treadmill exercise for 1 h to induce DOMS. After the exercise, the subjects will take either JGT or a placebo for 3 days. After a more than 1 week wash-out period, the subjects will repeat the same process with the other drug. Pain intensity, calf circumference, and pain threshold will be measured as outcome measures. Blood tests and blood pressure will be measured as safety assessments. In addition, blood tests for muscle damage and inflammation markers, such as creatine kinase, interleukin-6, and C-reactive protein, will be analyzed.

**Discussion:**

This will be the first trial to assess the effect of JGT on exercise-induced muscle soreness. Our findings will provide valuable data to determine the clinical effects of JGT on DOMS.

**Trial registration:**

Clinical Research Information Sevice, KCT0003457. Registered on 29 January 2019.

## Background

Muscle soreness after exercise, known as delayed-onset muscle soreness (DOMS), occurs after long-term physical activity or unusual exercise [1, 2]. DOMS symptoms, such as pain, discomfort, muscle tenderness, or loss of range of motion, usually occur 12–48 h after exercise and mend within 7 days. DOMS symptoms occur when structural damage to the muscle fibers initiates an inflammatory reaction cascade, which consequently increases inflammatory markers and intramuscular enzymes, such as creatine kinase (CK) [2, 3]. However, the mechanism of DOMS after exercise has not been fully elucidated. Although symptoms disappear over time, eccentric activity may cause significant changes to muscle function and may increase the risk of sports injuries [2]. Analgesics can be used for severe pain, but some studies have demonstrated a lack of efficacy of non-steroidal anti-inflammatory drug treatments [4, 5]. Many studies have attempted to identify ways to alleviate DOMS symptoms, such as massage, cryotherapy, cold-water immersion, and laser acupuncture [6–11]. Various supplements with anti-inflammatory and antioxidant effects have been studied to help recovery after exercise [12–14]. Moreover, there has been increasing interest in herbal medicines to treat DOMS because of their holistic approach and minimal side effects [15].

Jakyakgamcho-tang (JGT), also known as Shakuyakukanzoto, Shaoyaogancao-tang, or Peony licorice decoction, is an herbal medicine widely used to treat acute pain in both skeletal and smooth muscle [16, 17]. JGT is widely prescribed to treat muscle pain and cramps in traditional Korean and Japanese medicine [18, 19]. JGT consists of the herbs *Glycyrrhiza uralensis* Fischer (Glycyrrhizae Radix et Rhizoma) and *Paeonia lactiflora* Pallas (Paeoniae Radix), which contain glycyrrhetic acid, glycycoumarin, isoliquiritigenin, paeoniflorin, and albiflorin as active components [20]. Glycyrrhetic acid inhibits calcium-activated potassium channels, which consequently relax skeletal muscle, while paeoniflorin relaxes muscle fibers by regulating calcium movement near the neuromuscular junction [21, 22]. Another study reported that JGT reduces excess potassium ions from the external space of myofibers, thus reducing muscle pain [23]. Although *Glycyrrhiza uralensis* Fischer and *Paeonia lactiflora* Pallas have known analgesic and muscle relaxation effects, respectively, studies have shown that there is a synergetic effect when both herbs are used together [24–26]. The analgesic effects of JGT have been reported in various animal studies [27, 28]. However, no clinical trials have evaluated the therapeutic effects of JGT on exercise-induced muscle pain.

The aim of this study is to evaluate the effect of JGT on pain reduction and improvements in muscle damage after exercise. The safety and effectiveness of JGT for DOMS symptoms will be demonstrated in a randomized, double-blind, placebo-controlled, crossover design clinical trial. After inducing DOMS with 1-h eccentric exercise, pain intensity, pain threshold in calf muscles, and calf circumference will be measured from 0 to 72 h after exercise along with blood tests for the safety analysis. Additionally, shifts in serum and urinary metabolites will be analyzed using a metabolomics-based analysis to provide insight into the pharmacological mechanism of JGT.

## Methods and design

### Objective

The aim of this study is to assess the therapeutic effect of JGT in the relief of DOMS symptoms. The primary outcome is the difference between the JGT and placebo groups in pain intensity, measured every 12 h from 0 to 72 h after exercise. Our secondary outcomes include the pain threshold in the calf muscles, calf circumference, and serum markers of muscle damage. Furthermore, exercise-induced shifts in serum and urinary metabolites will be analyzed using a metabolomics-based analysis.

### Study design

This study will be a randomized, placebo-controlled, crossover design, investigator-initiated clinical trial. The trial will be conducted at Pusan National University Korean Medicine Hospital. Thirty healthy male adults will be recruited via hospital bulletin boards and local advertisements. Subjects who voluntarily wish to participate in this study and provide written informed consent will undergo a screening assessment to determine their eligibility. Subjects will be hospitalized for 4 days. On the first day, the subjects will perform eccentric exercise for 1 h to induce DOMS. After exercise, the subjects will be administered either JGT or placebo for 3 days. After a more than 1 week wash-out period, the subjects will repeat the same process with the other drug. The duration of the wash-out period was calculated based on the major component of JGT with the longest half-life. As glycycoumarin has the longest half-life (*T*_1/2_) of 14.9 h [20], we decided that the wash-out period should be 6.21 days or more, which is 10 times the half-life of glycoumarin needed to minimize the carry-over effect of JGT. The overall study flow is shown in Fig. 1. A detailed schedule is given in Fig. 2 and Table 1.

**Fig. 1 Fig1:**
[figure not shown]
Flow chart of the study

**Fig. 2 Fig2:**
[figure not shown]
Schedule of enrollment, interventions, and assessments, according to the SPIRIT 2013 statement

**Table 1 Tab1:** Time schedule for the in-hospital clinical trial

Day	Day 1				Day 2				Day 3			Day 4			
Time points	15:00	17:00	18:00	19:00	00:00	6:00	12:00	18:00	6:00	12:00	18:00	6:00	12:00	18:00	19:00
Time after exercise		–1 h	0 h	1 h	6 h	12 h	18 h	24 h	36 h	42 h	48 h	60 h	66 h	72 h	
Blood pressure		○		○		○		○	○		○	○		○	
Check for adverse events				○		○		○	○		○	○		○	
Physical examination	○														
Body composition analysis	◎														
IPAQ-SF questionnaire	◎														
Treadmill exercise			○												
Medication				○		○	○	○	○	○	○	○	○		
Randomization			○												
Blood tests		○												○	
Serum CK analysis		○				○		○			○	○		○	
Serum CRP, IL-6		○	○	○	○	○		○							
Pain intensity assessments		○	○	○	○	○		○	○		○	○		○	
Calf circumferences		○	○	○	○	○		○	○		○	○		○	
Pain threshold		○	○	○	○	○		○	○		○	○		○	
Serum & urine collection		○		○										○	
Blind assessment															○

◎ Assess only at the first hospitalization (Phase I)

*IPAQ-SF* International Physical Activity Questionnaire-Short Form, *CK* creatine kinase, *CRP* C-reactive protein, *IL-6* interleukin-6

### Participants

#### Inclusion criteria

Subjects will be considered for inclusion who:
Have experienced muscle soreness with a numeric rating scale (NRS) score> 5 within 24 to 30 h after exerciseAre healthy male subjects from 19 to 35 years of age without any recognized diseaseHave a body mass index (BMI) > 18.5 kg/m^2^ and < 30 kg/m^2^Have not exercised regularly for 2 consecutive weeks or more in the last 6 months or moreHave voluntarily signed the written consent approved by the institutional review board (IRB) after sufficient explanation prior to the study.

#### Exclusion criteria

Subjects will be excluded if they:
Have had an open wound or inflammatory disease within the last 6 monthsHave neurological or muscular disorders that may affect muscle strengthAre missing limbsHave a seriously unstable medical condition determined from a physical examination, such as cardiovascular disease, respiratory disease, gastrointestinal disease, hepatobiliary disease, metabolic disease, endocrine disease, renal disease, urinary disease, or problems with the nervous system or mental healthAre taking steroids, analgesics, muscle relaxants, or other medications that the researchers decide to be inappropriate, such as antispasmodics, antidepressants, antidiarrheals, antibiotics, or thrombolyticsHave a history of alcohol abuse or drug abuse within the past yearHave taken other clinical trial drugs for less than 3 monthsHave genetic problems, such as galactose intolerance, Lapp lactase deficiency, or glucose-galactose malabsorptionAre unwilling or unable to follow the study guidelinesAre determined by the researcher to be inappropriate for this study.

### Randomization and allocation concealment

Subjects will be randomly allocated to either the JGT or the placebo group with equal probability. An independent statistician will use SAS version 9.4 software (SAS Institute, Cary, NC, USA) to generate a random allocation list and will send the list to the pharmaceutical company for packing. The random allocation list will assign 30 subjects to group A or B. According to the crossover design, both groups will take JGT and the placebo drug. Subjects in group A will take JGT and those in group B will take the placebo drug during their first hospitalization.

### Blinding

The statistician will send the randomization code to the pharmaceutical company for packing to maintain blindness in both the assessors and the subjects. JGT and the placebo drug will be manufactured by the same pharmaceutical company. The placebo drug will be manufactured in a form similar to that of the JGT. It was confirmed in advance that the taste and flavor will be similar. According to the random sequence, the drugs will be packed in the same form and will be delivered to the hospital. The pharmacist will supply the drug sequentially during the trial period, according to the randomization code. The blinding will be maintained until all 30 subjects have completed the study and the database is locked. To evaluate whether the blinding was successful, a quick questionnaire will be conducted at the end of each hospitalization, asking “Which test drug do you think you were allocated to, JGT or placebo drug? And why do you think so?”

### Exercise protocol for inducing muscle soreness

A standardized treadmill exercise protocol will be performed on the first day of hospitalization to induce DOMS. Previous studies have shown that a downhill running protocol induces stress in the gastrocnemius muscles, as it is an unfamiliar eccentric exercise [29–31]. The subjects will step backwards on a moving treadmill inclined at 13°. Starting with the right leg, the subjects will continue the exercise for 1 h at a speed of 2.2 km/h. The subjects will carry a 5–10 kg weight belt to ensure adequate stimulation to the muscles.

### Intervention

After the treadmill exercise, the subjects will be administered either JGT or the placebo drug three times daily before meals for 3 days (nine times in total). Both the JGT and placebo drug will be manufactured by Kyungjin Pharmaceutical Co., Ltd. (Gyeonggi-do, Republic of Korea) according to Good Manufacturing Practice guidelines. Both drugs will be prepared in the form of light brown granules. The constituents of each drug are shown in Table 2. After the first hospitalization, subjects will be readmitted to the hospital after the wash-out period of more than 1 week. During the second hospitalization, subjects will be administered the other drug, not the one they have taken before, in accordance with the crossover design. No over-the-counter drugs or prescription-based medicines will be permitted throughout the clinical trial. If a subject already has taken a medication during the trial or the subject is suffering from a medical condition that requires medication, the subject will be dropped from the trial.

**Table 2 Tab2:** Constituents of Jakyakgamcho-tang and the placebo control drug

Test drug	Constituents	Contents	Purpose of use
Jackyakgamcho-tang (JGT)		The amount contained in a single dose (3.0 g)	
	*Paeonia lactiflora* Pallas	2 g	Main components (used as a solid extract 480 mg)
	*Glycyrrhiza uralensis* Fischer	2 g	
	Lactose	1650 mg	Excipient
	Cornstarch	720 mg	Excipient
	Colloidal silicon dioxide	150 mg	Excipient
Placebo		The amount contained in a single dose (3.0 g)	
	Lactose	1800 mg	Excipient
	Cornstarch	785 mg	Excipient
	Colloidal silicon dioxide	160 mg	Excipient
	Caramel color	255 mg	Coloring

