### Statistical analysis

The statistical analysis will be conducted by an independent statistician using SAS version 9.4 (SAS Institute). The significance level will be set at 0.05 in a two-tailed test. All continuous data will be presented as means and 95% confidence intervals (CIs). Categorical data will be reported as frequencies and percentages. The intention-to-treat (ITT) principle will be applied for the primary analysis. The ITT population will include subjects who meet the full analysis set (FAS) criteria, including subjects who had the primary outcomes assessed once or more except for the baseline measures and who took the test drug at least once. Subjects who do not meet the eligibility criteria, those who did not take the test drug throughout the study, and those who have never been evaluated after the screening visit will be excluded from the FAS dataset. The per-protocol set will also be analyzed, which will only include subjects who have completed the study as a supplementary analysis.

The baseline characteristics of the study subjects will be presented using a descriptive analysis for each group. The primary outcome will be the differences between the VAS score with motion measured at various intervals from 0 to 72 h after exercise. A mixed-effect model for repeated measures (MMRM) will be used to assess differences along with the time effect. The dependent variable will be the change in the VAS score (pain with motion) measured from 0 to 72 h after exercise. The model will include treatment and protocol-specified visits as fixed effects, and subjects as a random factor. Dunnett’s test will be used for multiple comparisons. The results of the secondary effective analysis will be analyzed using the same method as for the primary outcome, in the case of continuous variables with time variation. Additionally, Student’s *t* test or Wilcoxon’s signed-rank test will be used to compare results before and after the treatment within each group. Categorical data will be analyzed using the chi-squared test or Fisher’s exact test. Missing values by maximum likelihood will be considered when the MMRM is used. The last observation carried forward method will be adopted for missing values for Student’s paired *t* test, the Wilcoxon signed-rank test, or repeated measures analysis of variance.

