## Discussion

This is a protocol for a randomized, double-blind, placebo-controlled, crossover-designed clinical trial to study the efficacy and safety of the herbal medicine JGT in the relief of DOMS in healthy male adults. The strength of this study lies in the rigorous design. In general, DOMS is difficult to test in a clinical trial because of the short duration of the symptoms. A standardized method for pain induction and a rigorously designed clinical trial will provide reliable results on the therapeutic effects of JGT in DOMS. The Standard Protocol Items: Recommendations for Interventional Trials (SPIRIT) checklist is attached as Additional file 1. This study will provide a better understanding of the mechanisms of JGT for relieving muscle pain in general, as DOMS is an important experimental model to evaluate analgesic efficacy and to study movement-related pain [40, 41]. We expect to provide novel insights into potential biological mechanisms of JGT through a metabolomics approach. In this protocol, the inclusion criteria of the study participants will be narrowed to male adults, and participants will be hospitalized during the intervention. Therefore, the results of the metabolomics analysis are expected to yield reliable results, because factors affecting metabolites, such as age, gender, and food intake, will be controlled [42, 43]. Moreover, as this is a 2 × 2 crossover design study, each subject will serve as his own control to reduce individual variations.

To our knowledge, no clinical trial has evaluated the therapeutic effects of JGT on exercise-induced muscle pain. Several clinical trials have evaluated the antispasmodic and analgesic effects of JGT. Clinical trials of JGT to reduce pain have mostly considered pain caused by complications, such as muscular cramps of patients on hemodialysis and myalgia caused by chemotherapy [44–48]. Although it is widely prescribed to manage muscle soreness and myalgia, it is difficult to find any evidence other than a clinical study about JGT on painful muscle cramps in patients with lumbar spinal stenosis [49]. A retrospective case series study with 37 patients treated with JGT for muscle spasms and pain was published in 2004 [16]. However, the current clinical trial will be the first to assess the effect of JGT on exercise-induced muscle soreness. This study will provide valuable data to determine the clinical effects of JGT on exercise-induced pain.

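### Dropping a subject from the whole trial for any medication, even in the wash-out, gives up within-subject comparisons that postponing the second admission would keep; the cost is modest

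*Protocol article*

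**What the plan says.** Protocol article, Intervention: "No over-the-counter drugs or prescription-based medicines will be permitted throughout the clinical trial". There is no exception by type of medicine, dose or timing. Two triggers lead to removal. One is intake ("If a subject already has taken a medication during the trial"). The other is need ("the subject is suffering from a medical condition that requires medication, the subject will be dropped from the trial"). The consequence is loss from the trial, not from one treatment period.

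The same section sets only a lower limit for the gap between admissions: "subjects will be readmitted to the hospital after the wash-out period of more than 1 week". The wash-out lies between the two admissions, so the ban covers it although it is not named.

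The Discussion gives the reason for the 2 × 2 crossover: "each subject will serve as his own control to reduce individual variations".

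Statistical analysis keeps in the full analysis set any eligible subject with one dose and one post-baseline primary score. For the primary mixed model it says: "Missing values by maximum likelihood will be considered when the MMRM is used". The per-protocol set is the one "which will only include subjects who have completed the study as a supplementary analysis". For the paired tests and repeated measures analysis of variance: "The last observation carried forward method will be adopted for missing values".

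**The concern.** The ban lasts for two 4-day admissions plus a wash-out of more than 7 days: 4 + 7 + 4, so more than 15 days. More than 7 of them are spent outside hospital, where an unrelated tablet for a cold or headache is most likely. Such a tablet cannot affect the 72 h of period 1 scores already taken, and a later readmission would let it clear before period 2. Removing the subject nevertheless loses the second period, and with it the own-control comparison on which the design rests.

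In hospital the trade is closer, because a medicine could alter pain, CK, CRP, IL-6 and metabolites. Even so, the remaining assessments are already scheduled in an inpatient, and a completers-only set already exists from which such subjects can be left out.

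At stake is mainly the width of the interval for JGT against placebo. If analgesic use follows the pain being measured, a smaller question of bias arises as well.

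A separate matter in the same area is carrying the last score forward in the paired tests. The Background says soreness appears at 12–48 h and mends within 7 days, so a score taken near the peak does not describe pain at 72 h.

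**Working it through.** **Scores lost.** Post-exercise VAS is taken at 0, 1, 6, 12, 24, 36, 48, 60 and 72 h (Outcome measures, Pain intensity): 9 per period, 18 per subject. If assessment ends at the drop:

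- wash-out: 9 of 18 lost;
- period 1, just after the 24 h score: 4 + 9 = 13 of 18 lost;
- period 2, just after the 24 h score: 4 of 18 lost.

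**Precision.** N = 30 is from the article. The within-subject correlation ρ and the number of drops k are assumptions, because the article gives no correlation, SD or drop rate. Treat each period as one summary value with unit variance. A complete pair carries information 1/[2(1 − ρ)] on the treatment difference. With k single-period subjects split equally by drug, those subjects together carry k/4. Multiplying the total by 2(1 − ρ) gives the equivalent number of complete pairs:

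n_eq = (30 − k) + k(1 − ρ)/2, variance ratio = 30/n_eq.

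A full generalised least squares calculation with a period term, for even k, gave the same information.

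| Drops k | n_eq, ρ = 0.3 / 0.5 / 0.7 | Variance ratio | Completers only, 30/(30 − k) |
|---|---|---|---|
| 1 | 29.35 / 29.25 / 29.15 | 1.022 / 1.026 / 1.029 | 1.034 |
| 3 | 28.05 / 27.75 / 27.45 | 1.070 / 1.081 / 1.093 | 1.111 |
| 6 | 26.10 / 25.50 / 24.90 | 1.149 / 1.176 / 1.205 | 1.250 |

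A drop partway through period 1 leaves less than a full single period, so its cost lies between the two ratios. An assumed risk per subject of 2%, 5%, 10% or 20% means 0.6, 1.5, 3 or 6 drops among 30.

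**The sample-size statement.** The Sample size section says no calculation was possible and borrows 15 per arm at 90% power and two-sided 5% from a pilot-study rule. The article gives no effect size, so 30 cannot be reproduced. Solving backwards (noncentral t, 28 df), 15 per arm in a parallel comparison detects 1.23 SD. In this crossover all 30 subjects take both drugs. For 1.23 SD, the paired standardised difference is 1.23/√[2(1 − ρ)] = 1.04, 1.23 or 1.58 for ρ = 0.3, 0.5 or 0.7. With 24 complete pairs, power exceeds 99% in each case.

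**Bias when pain drives the drop.** This is a simulation with one score per period and every input assumed: placebo mean 50 mm, SD 20 mm, true effect −10 mm, and 80% of subjects above a threshold of 70–90 mm taking an analgesic and being dropped.

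- Completers: the estimate is −8.4 to −9.8 mm over ρ 0.3–0.7, which is 2–16% towards zero, with about 5 down to 0.6 drops per 30.
- Random-subject likelihood model, threshold 75 mm, ρ = 0.5, about 3 drops: −10.0 mm if the high score is recorded before the drop, −9.0 mm if that period's score is lost.
- No true effect, completers (threshold 75 mm, ρ = 0.5): shift of 0.03 mm, which is negligible.
- Drops unrelated to pain, completers: −10.0 mm, so precision alone suffers.

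**Carrying forward.** Assumed placebo VAS curve of 20, 20, 25, 35, 55, 58, 50, 38 and 25 mm, scores held to 0–100 mm, and drops unrelated to pain with the last score at 12–60 h (20,000 simulated groups of 30). The 72 h group mean moves from 26.0 to 26.7 mm with 1 drop and to 28.1 mm with 3.

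**The case against.** The strongest reply is that the rule is coherent. Stopping at medication and using likelihood targets the effect without other medicines, a fair aim for a 72 h mechanistic trial with inflammatory markers and untargeted metabolomics. Putting medicated scores into the primary model is a choice of estimand with its own cost. That stands. It is why the fix asks the sponsor to name the primary version in advance, rather than insisting that all scores be used. It does not answer the wash-out case, where postponement leaves both periods free of other medicines. Not repeating a weighted treadmill hour in someone who is ill is also fair, and the fix requires fitness to exercise.

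Second, few drops are likely: the subjects are healthy men aged 19–35, users of analgesics and similar drugs are excluded, and 8 of the 15 or more days are in hospital. This stands and limits the size of the point.

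A reader might infer more than the article supports:

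- *That 30 subjects leave no room for drops, because 30 = 2 × 15.* The 15 is per arm, and here each treatment has 30 subjects. The article sets no crossover effect size against which a margin could be judged.
- *That the rule biases the primary analysis.* The full analysis set and the likelihood model keep data up to the drop. In the simulation the likelihood estimate is protected when the high score is recorded first. Some bias remains possible if it is not.
- *That all follow-up certainly ends.* This is the natural reading, but withdrawal procedures may stand in the full protocol, which is not shown.

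**Conclusion.** The point holds as a minor one. The rule as written removes a subject from the whole trial for any medicine at any time. A drop in period 1 or the wash-out loses that subject's within-subject comparison, although deferral would protect the endpoints. The prohibition itself is sound.

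The cost is mainly precision and is small per subject. Three drops leave the equivalent of 27 to 28 complete pairs, and six leave about 25 to 26. These figures rest on assumed correlations, on single-period data being kept, and on drop counts the article does not give.

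Drops driven by pain could pull the estimate towards no difference, chiefly in the completers-only set. The size depends wholly on assumed inputs.

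The carrying-forward point is separate and also small. It affects the supplementary paired tests, not the primary model, and does not arise after a wash-out drop, where period 1 is complete and period 2 has no score to carry.

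**What to change.** Keep the ban and replace removal from the trial with wording such as:

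> Any medicine taken is recorded with dose and time. After medication in period 1 or the wash-out, the second admission is postponed until the medicine has cleared, and takes place if the subject is fit to exercise. After medication in hospital, scheduled assessments continue unless consent is withdrawn.

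Report the primary mixed model with and without post-medication values from that hospitalisation, stating in advance which is primary. Exclude such subjects only from the per-protocol set. In the paired within-group tests, replace carried-forward scores with observed values or with the mixed-model change at each time.

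**Cost.** A short amendment, a few later second admissions and no new assessments. Some later values will be influenced by the medicine. If it lowered VAS by an assumed 10–20 mm in one of 30 placebo subjects, the placebo mean at those times would fall by 10/30 to 20/30, or 0.3–0.7 mm (three subjects: 1.0–2.0 mm), towards no difference. Comparing the two versions of the model shows this.

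Trial status expected completion by August 2019. If enrolment has closed, only the change to the paired tests and a listing of drops by drug, period and hour still apply.
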